### Effectiveness

For the effectiveness, a baseline measurement will be performed in all participating clinics, including guideline adherence on TEM, and a range of organizational, professional, and patient characteristics (see outcome measures). Following baseline measurement, the multifaceted implementation strategy will be applied in the intervention clinics. After ten to twelve months of intervention exposure, the after measurement will be performed again in all 25 participating clinics.

### Process evaluation

A process evaluation, according to Hulscher *et al.*[21], will be performed during and after the intervention to investigate the feasibility of the implementation strategy.

### Intervention

The multifaceted implementation strategy, based on a barrier analysis among professionals and patients, will focus on three different levels: patient, professional, and organizational level [20]. The three levels and all associated tools are successively described here.

### Patient level

We will develop patient educational materials in three different forms, a patient information leaflet, posters, and a website.

The patient information leaflet will provide general background information on the fertility work-up procedure, prognostic factors that influence the chance on spontaneous conception, (dis)advantages of expectant management, and (dis)advantages of fertility treatment. In every intervention clinic, posters with information on the prognostic model and expectant management will be placed in the waiting areas. In the leaflet and on the posters, patients can find a code which is needed to gain access to the website. There is a different code for each intervention clinic. The website will give more individualized information by access to a digital version of the prognostic model of Hunault [5]. Herewith, patients can calculate their chances of natural conception within one year and experience the influence of altering characteristics. It will also provide additional information on the basic fertility workup, the chance of natural conception versus the chance of conception after fertility treatment, (dis)advantages of expectant management, and (dis)advantages of fertility treatment. Furthermore, it advises patients what they can do to optimize their chances of spontaneous conception during the expectant management period, *e.g.*, information on intercourse timing and frequency, weight regulation, and lifestyle. This information will be in accordance with the information provided in the Dutch national network guideline on infertility [10].

This information material will be developed according to the International Patient Decision Aids Standards criteria for the dimensions ‘information’ and ‘probabilities’ [22], as well as according to the American Medical Association criteria [23].

### Professional level (*e.g.*, gynecologists (in training), fertility doctors, and GPs)

The strategy regarding the professionals contains audit and feedback, an education outreach visit, supportive consultation tools, and a video-based communication training.

The audit and feedback of the current care will consist of a feedback report based on the results of the baseline measurement. This feedback will report clinic’s guideline adherence on TEM in a twelve-month period prior to the randomization compared with the other participating clinics. It will give insight in how they are adhering to the guideline concerning the policy for couples with unexplained or mild infertility, *e.g.*, use of prognostic models and subsequent TEM in case the prognosis is good. Furthermore, the report will provide feedback on patient-related measures like general experiences with fertility care, specific experiences with the prognostic model and TEM, quality of life, and trust in their physician [ref].

In addition to this audit and feedback, an educational outreach visit will take place with fertility doctors and gynecologists (in training), in which background information about how and when to use the prognostic model of Hunault, and subsequent TEM will be given and in which the results of the baseline measurement and local barriers will be discussed. The result of this visit will be an individualized action plan per clinic.

The supportive consultation tools are developed containing a digital version of the prognostic model of Hunault on a website and we will provide professionals with a summary of the guideline on TEM in the form of a pocket card.

Finally, a video-based training strategy will be provided to improve the communication techniques to counsel the patients on their chance of spontaneous conception versus conception after treatment, the (dis)advantages of expectant management versus fertility treatment, and on the reason for TEM (*i.e.*, making clear it is not a waste of time). Consistent with functional models of medical communication described in the field [24], the LEAPS Framework, a pneumonic for Listen, Educate, Assess, Partner and Support will be used to develop the intervention [25].

### Organizational level (GP units and fertility clinics)

During the educational outreach visits an example of an up-to-date local protocol will be offered to the fertility clinics that do not already have an updated protocol available. This local protocol will be based on the Dutch network guideline on infertility, and it will focus on the initial fertility assessment (diagnostics), identification of patients with mild or unexplained infertility, the use of the prognostic model of Hunault, and TEM [10]. The clinics can adjust this protocol to their own lay out and they can distribute it either in the form of a hard copy or digital copy, depending on the preference of the professionals.

Furthermore, we will provide the GPs allied to the intervention clinics with feedback on their referral behavior, *e.g.*, were patients referred according to the guideline recommendations.

### Study population/participants

To include a representative patient group, we will select potential participating couples retrospectively in each clinic by means of the clinics’ financial registration database (Diagnosis Treatment Combination code). In this nationwide registration system, patients undergoing diagnostics or treatment for infertility are identified with a specific fertility code (F-code). For the baseline measurement, we will invite couples that were given the code for new fertility patients (F-11) between February 2011 to March 2012 to participate in this study. For the after measurement, we will invite the couples that were given the F-11 code during the ten- to twelve-month intervention period. We will invite couples to participate by giving their permission for a medical record study and filling out a questionnaire.

The couples are eligible to participate when they have been diagnosed with unexplained or mild infertility, have a good prognosis (>30%) according to Hunault’s prediction model, did not have previous fertility treatment, and the female age is between 18 and 38 years. Couples with bilateral tubal pathology, severe male factor, or anovulation are not eligible to participate.

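### After-period couples are identified and invited once their clinic's arm is known and the strategy is at work, so the adherence denominator could be selected differently by arm

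*Protocol article*

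**What the plan says.** All references are to the protocol article.

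- **Timing.** Under Randomization, clinics are told their allocation in person. Under Study population/participants: "For the after measurement, we will invite the couples that were given the F-11 code during the ten- to twelve-month intervention period". These couples therefore present after allocation is known.
- **Sampling frame.** "we will select potential participating couples retrospectively in each clinic by means of the clinics’ financial registration database". The frame is the code for new fertility patients (F-11), used in the same way in both arms and both periods.
- **Entry by diagnosis.** "The couples are eligible to participate when they have been diagnosed with unexplained or mild infertility"; a Hunault prognosis above 30% is required as well. Couples with these characteristics are also the denominator of the primary adherence rate (Primary outcome effectiveness).
- **Entry by invitation.** "We will invite couples to participate by giving their permission for a medical record study and filling out a questionnaire".
- **What the strategy changes.** Under Organizational level, the example protocol covers "identification of patients with mild or unexplained infertility, the use of the prognostic model of Hunault, and TEM", as well as the initial work-up; also, "we will provide the GPs allied to the intervention clinics with feedback on their referral behavior". Under Patient level and Professional level, couples receive a leaflet, posters and a website on expectant management, and professionals are trained to counsel in its favour.
- **Analysis.** Under Data analysis, the main outcome is compared by a chi-square test. Regression models are described for the relative contribution of the strategy and other predictors of adherence.

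**The concern.** Randomising clinics makes the arms comparable at clinic level. It does not guarantee comparable couples when the couples are found and recruited afterwards. Two entry steps come after allocation.

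The first is diagnosis. If intervention clinics work up couples differently or recognise unexplained or mild infertility more readily, the set of couples counted as eligible changes. The adherence percentage then moves through its denominator, even if no individual decision changes.

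The second is participation. Couples are approached retrospectively, after contact with the strategy and possibly after they have chosen between waiting and treatment. Part of the questionnaire concerns their experience with the prognostic model and expectant management, and their trust in their doctors. Whether a couple takes part may therefore depend on the outcome itself, and more strongly in one arm.

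At stake is whether a difference in the primary percentage reflects adherence or the make-up of the sample. The article states no safeguard at either step.

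**Working it through.** **1. Scale of the trial (Sample size).** Inputs: 60% v 80%, ICC 0.1, alpha 5%, 25 clusters, 450 couples, so 450/25 = 18 per clinic. Two-sided testing and 80% power are assumed, because neither is stated.

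- Per arm without clustering: (1.96·√(2·0.7·0.3) + 0.842·√(0.6·0.4 + 0.8·0.2))² / 0.2² ≈ 81.2, rounded up to 82.
- Design effect: 1 + (18 − 1)·0.1 = 2.7.
- Total: 2·82·2.7 = 442.8, which agrees with 450 to within 3%. The effective sample size is 450/2.7 ≈ 167.

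The planned figure is not in dispute. It gives the 20-point target against which a selection effect can be judged.

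**2. Participation step.** The article gives no response rates, so every rate here is an assumption. With true adherence p, and response rates a among adherent and b among non-adherent couples:

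observed adherence = p·a / (p·a + (1 − p)·b)

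For p = 0.60 in the intervention arm:

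- 60% v 50% response: 0.36/(0.36 + 0.20) = 64.3%.
- 60% v 40% response: 0.36/(0.36 + 0.16) = 69.2%.

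Only the ratio r = a/b matters. With no true effect and r = 1 in the control arm:

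| r, intervention arm only | observed adherence | false difference | chance of a significant result |
|---|---|---|---|
| 1.1 | 62.3% | 2.3 points | 6% |
| 1.25 | 65.2% | 5.2 points | 11% |
| 1.5 | 69.2% | 9.2 points | 24% |
| 2.0 | 75.0% | 15 points | 55% |

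The last column is a normal approximation with 167/2 effective couples per arm, so clustering is already allowed for.

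**3. The same response pattern in both arms.** With 60% v 40% response in each arm:

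- No true effect: both arms show 69.2%, and the false difference is zero.
- True 60% v 80%: the control arm shows 69.2% and the intervention arm 0.48/(0.48 + 0.08) = 85.7%. The difference is 16.5 points instead of 20, a bias toward the null.

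**4. Diagnosis step.** Suppose a fraction f of the intervention-arm sample is newly labelled with adherence q, and the rest stay at 60%: observed = (1 − f)·0.60 + f·q. For f from 0.1 to 0.3:

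- q = 0.30: 57% down to 51%.
- q = 0.90: 63% up to 69%.

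The shift can go either way.

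**5. Can the stated analysis remove it?** Subtracting baseline helps only with selection that is stable over time within an arm. Selection produced by the strategy arises only in the after period. Regression among participants can adjust for measured characteristics, but not for taking part because of the decision made.

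**The case against.** Several points on the other side are sound.

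- **The questionnaire.** A reader might infer that a couple enters the primary analysis only if it returns a questionnaire. The article does not say this. One invitation covers two things, and the Data collection section treats records and questionnaire as separate sources. Chart-only inclusion may already be intended.
- **The score.** A reader might infer that the clinic's own Hunault calculation decides entry. The text asks for a good prognosis under the model and does not say who computes it. The feedback report is to show clinics how far they use prognostic models, which would mean little if only couples scored by the clinic could enter. Calculation by the researchers is the more coherent reading. The diagnosis, however, still rests on the clinic's work-up.
- **The frame.** An administrative code applied alike in both arms limits hand-picking by clinics. It does not reach the later steps of diagnosis and permission.
- **Strength of the push.** The example protocol is adjustable and goes only to clinics without an updated one, so a change in diagnostic practice is possible but not shown.
- **Size.** A reader might take 9 points as the expected bias. It needs a differential response assumed in the intervention arm alone, and step 3 shows zero or a bias toward the null under a common pattern.
- **Timing.** Baseline measurement is already running (Trial status), so changing the rules for the after period alone would disturb the before-after comparison.

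What stands is that couples present, are diagnosed and are invited after allocation, while the strategy acts on work-up, identification and attitudes. Reporting of participant flow and weighted sensitivity analyses are ordinary content of an analysis plan that is not shown, and their absence is not held against the article.

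**Conclusion.** The risk of selection after randomisation is real and follows from the entry route that the article itself fixes. It concerns the denominator of the primary outcome, and the stated analyses cannot remove it. Neither direction nor size is established. The figures of 64% to 69% for a true 60% rest on assumed response rates and on no differential response in the control arm. The documents do not support a claim that non-returners of the questionnaire are excluded, that clinic scoring decides entry, or that the result will be biased by a particular amount. The point calls for an inexpensive safeguard or, if the safeguard is already intended, for it to be stated.

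**What to change.** In Study population/participants, state that:

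1. Study abstractors, blinded to arm where feasible, apply the entry criteria and calculate the Hunault score from raw chart data. They do so in the same way in both arms and both periods, whether or not the clinic labelled or scored the couple.
2. Permission for the record study alone is enough for inclusion in the primary outcome. The questionnaire is needed only for patient-reported outcomes.
3. The same rules apply to the baseline sample now being collected, so that the before-after comparison stays like with like.

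**Cost.** Slightly more abstraction work, and fewer questionnaires per analysed couple. Acting while baseline collection is still under way limits the disruption. Selection on record permission itself would remain, as would any effect of the strategy on the work-up recorded in the chart. Both should be acknowledged as limitations.

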### Sample size

The expected adherence to TEM in the control arm is estimated based on previous studies at 60% [11]. To increase this to 80% with an intra-class correlation (ICC) of 0.1, alpha at 5%, comparing two strategies, we estimate that with 25 clusters we would need a total sample size of 450 patients. This means we need to include 15 to 20 patients per clinic in the baseline as well as in the after measurement.

## Outcome measures

### Primary outcome effectiveness

The primary outcome measure of the proposed study for effectiveness will be the guideline adherence rate on TEM: the percentage of couples that are eligible for TEM (couples with mild or unexplained infertility with a prognosis of >30% of natural conception within one year) who actually agree upon the expectant management period of at least six months after the initial fertility assessment is concluded.

### Secondary outcomes effectiveness

1. Treatment-related measures: time to the start of fertility treatment and the number and types of fertility treatments that the couples received.

2. Treatment outcome-related measures: (ongoing) pregnancy rate, miscarriage, extra uterine gravidity, multiple pregnancy rate, and time to pregnancy.

3. Patient-related outcome measures : general experiences with fertility care such as information provision, respect for patients’ values and accessibility of care (to be measured with Patient Centeredness Questionnaire Infertility) [26], specific experiences with the prognostic model and TEM, quality of life (estimated by FertiQoL)[27], and trust in physician (measured by Wake Forest Trust Scale) [28].

4. Process related measures: percentage transition of patients to another fertility center.

5. Background characteristics that could influence guideline adherence (*e.g.*, age, referral status, type of infertility, duration and cause of infertility).

### Outcomes process evaluation

1. Actual ‘exposure’ of patients and physicians to the different elements of the implementation strategy.

2. How frequently the website has been visited by patients and physicians.

3. Experiences of patients and physicians with the different elements of the implementation strategy.

## Data collection

### Effectiveness

Data collection will be performed from medical records and a patient questionnaire.

Data abstraction from medical records will be performed using a standardized audit form. We will collect the background characteristics, treatment related measures, treatment outcome-related measures, and process-related measures.

The questionnaire will be divided into four parts. The first part consists of background questions (*e.g.*, highest educational level, country of birth). The second part regards the patients’ experience with the prognostic model and TEM as well as the patients’ trust in both the GP as well as the fertility doctor/gynecologist. The third part is the Patient-Centeredness Questionnaire-Infertility, a validated instrument measuring patient-centeredness of fertility care by asking about patients’ experiences with care. The last part is the FertiQol questionnaire, We will only use the Core module, which involves questions about mind-body, emotional, relational, and social aspects.

### Process evaluation

For the process evaluation, we will approach the local investigator during the intervention period to provide us with feedback about the implementation strategy. We will also keep track of how often the website is visited by logging data. At the end of the ten- to twelve-month intervention period, we will evaluate the strategy by means of a professional questionnaire and an addendum to the patients’ questionnaire in the after measurement.

### Data analysis

To analyze the effectiveness of the implementation strategy, descriptive statistics and multilevel analysis will be used. The statistical analysis will be performed using SPSS version 16.0 for Windows.

The main outcome, the difference in baseline and after-measurement scores in guideline adherence on TEM, between the intervention and control group will be analyzed with the chi-square test.

Descriptive analysis will be used to assess the difference in treatment-related, treatment outcome-related, and patient-related measurements between the intervention and control group. Furthermore, time to pregnancy and time to start fertility treatment will be analyzed using Kaplan Meier analysis with log-rank test. Univariate and subsequent multivariate logistic and Cox regression analyses will be used to analyze the relative contribution of the implementation strategy versus other predictive factors for guideline adherence on TEM.

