### Economic evaluation

We plan an economic evaluation alongside the clinical trial to investigate the cost-effectiveness of the multifaceted implementation strategy to improve guideline adherence on TEM. This economic evaluation compares the multifaceted implementation strategy to usual care and is done from a societal perspective. A distinction will be made between costs of the development and introduction of the implementation strategy and the costs of maintaining the implementation strategy. The input of resources is assessed by collecting volumes of consumed resources (*e.g.*, medical interventions like number IUI and IVF cycles and treatment related outcomes like ovarian hyperstimulation syndrome and multiple pregnancies) and multiplied by reported or guideline prices according to Oostenbrink [29]. To assess non-medical and indirect costs, we will build on the data collection and cost calculation frameworks from previous cost studies on IUI and IVF [30,31]. The incremental costs, expressed as costs/percentage guideline adherence to TEM, are determined by the differences in resource consumption and adherence rates between the intervention group and the control group. Robustness of the results (costs and health outcomes) for various assumptions and parameters estimates will be explored in sensitivity analyses and visualized in incremental cost-effectiveness ratio graphs and cost-effectiveness acceptability curves.

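### The 450 is sized for a single-wave comparison of 60% v 80%, but the main outcome is a difference in change between two separate samples of couples; adjusting for clinic baseline adherence resolves the mismatch

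*Protocol article*

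**What the plan says.** All references are to the protocol article.

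- **Sample size.** Control adherence is taken as 60%. The target is given as "To increase this to 80% with an intra-class correlation (ICC) of 0.1, alpha at 5%, comparing two strategies", and "we estimate that with 25 clusters we would need a total sample size of 450 patients". The section adds that "we need to include 15 to 20 patients per clinic in the baseline as well as in the after measurement". It gives no power, no variance term for the baseline wave and no correlation between waves.
- **Study population/participants.** The baseline wave consists of couples coded as new fertility patients before the intervention. For the second wave, "we will invite the couples that were given the F-11 code during the ten- to twelve-month intervention period". The waves are therefore different couples from the same clinics.
- **Primary outcome effectiveness.** The outcome is simply the percentage of eligible couples who agree to expectant management of at least six months.
- **Data analysis.** The contrast to be tested is "The main outcome, the difference in baseline and after-measurement scores in guideline adherence on TEM", between the intervention and control group, by chi-square. Multilevel analysis is named for effectiveness in general, without a model.
- **Economic evaluation.** Incremental costs per percentage adherence "are determined by the differences in resource consumption and adherence rates between the intervention group and the control group". No wave is named.

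**The concern.** The sample size and the main analysis address different contrasts. Subtracting a baseline measured in other couples brings in that wave's sampling error. No within-couple pairing cancels it; only stability of each clinic's adherence level between waves can. If that stability is modest, a trial sized for about 80% power is left with much less for the contrast it declares as its main outcome.

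The named test adds a second problem. An ordinary chi-square test compares proportions between groups of independent observations. It does not test whether one change differs from another, and it ignores clustering, although the sample size allows for an ICC of 0.1.

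**Working it through.** **Inputs from the article:** 60% v 80%; ICC 0.1; alpha 5%; 25 clinics; 450 patients; 15 to 20 per clinic in each wave.

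**Assumptions:** two-sided test; 12 control v 13 intervention clinics (no ratio is stated); baseline adherence 60% in both arms; between-wave correlation of clinic levels c, run from 0 to 1.

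**1. Reproducing the 450**

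- Two proportions, 80% power, pooled variance under the null: n = [1.960·√(2·0.7·0.3) + 0.842·√(0.24 + 0.16)]² / 0.20² = 81.2, so 82 per arm.
- 450/25 = 18 per clinic, inside the stated 15 to 20 per wave, so 450 is a per-wave figure.
- Design effect: 1 + 17 × 0.1 = 2.7.
- Total: 2 × 82 × 2.7 = 443, within 2% of 450. At 450 the same method gives 81% power. A target of 90% would need 589.

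The 450 is thus explained by one wave and two arms at about 80% power.

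**2. After-measurement alone, 18 per clinic**

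- Variance factor per clinic: F = 0.1 + 0.9/18 = 0.15.
- Variance = 0.24 × 0.15/12 + 0.16 × 0.15/13 = 0.004846; SE 0.0696.
- Power = Φ(0.20/0.0696 − 1.96) = 82%.

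**3. Change contrast**

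Baseline p(1−p) is 0.24 in both arms; after-measurement p(1−p) is 0.24 (control) and 0.16 (intervention).

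- Control: [2 × 0.24 × 0.15 − 2c × 0.1 × 0.24]/12
- Intervention: [(0.24 + 0.16) × 0.15 − 2c × 0.1 × √(0.24 × 0.16)]/13
- Sum: 0.010615 − 0.007015c

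**4. After-measurement adjusted for clinic baseline**

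The correlation of observed clinic proportions is r = 0.1c/0.15, and the variance is 0.004846 × (1 − r²).

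| c | Change: variance | Ratio to after-only | Change: power | Adjusted: variance | Adjusted: power |
|---|---|---|---|---|---|
| 0 | 0.010615 | 2.19 | 49.2% | 0.004846 | 81.9% |
| 0.5 | 0.007108 | 1.47 | 66.0% | 0.004308 | 86.2% |
| 0.7 | 0.005705 | 1.18 | 75.4% | 0.003791 | 90.1% |
| 0.8 | 0.005004 | 1.03 | 80.7% | 0.003468 | 92.5% |
| 1 | 0.003601 | 0.74 | 91.5% | 0.002692 | 97.1% |

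The change contrast matches the after-only comparison at c = (0.010615 − 0.004846)/0.007015 = 0.82 and is better above that.

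**5. Sensitivity**

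- With 15 to 20 per clinic, change-contrast power is 47–51% at c = 0, 62–68% at 0.5 and 86–94% at 1.
- A beta-binomial simulation (20,000 replicates, cluster-level t-tests and analysis of covariance, 18 per clinic) gives 46%, 63% and 77% for the change contrast at c = 0, 0.5 and 0.8. Baseline adjustment gives 76%, 81% and 89%, and after-only about 78%. At c = 0 adjustment costs about 2 points against after-only (75.7% v 77.5%), at 0.25 about 1 point.

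**The case against.** **The power loss is conditional.** This stands. The article gives no between-wave correlation. The same clinics observed in successive periods may be quite stable, and at about 0.8 or above nothing is lost. A reader might infer that the trial will have only 50 to 65% power, or that the change contrast has twice the planned variance; neither is supported. Those figures belong to correlations of about 0 to 0.5 and of about 0 respectively.

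**No power is stated.** Also true. About 80% is inferred because 450 reproduces there. The same 450 per wave would give the change contrast about 81% at a correlation of 0.8, but the Sample size section mentions no such correlation.

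**Multilevel analysis is named, and model detail belongs in an analysis plan.** This stands in part: random effects and covariates may be left to that plan. But the article itself fixes both the contrast and the test for the main outcome. Putting the same change contrast into a multilevel model would handle clustering without recovering the precision lost.

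**The powers above are not those of the chi-square test.** Correct. They assume an analysis that respects clustering; the test's unsuitability is a separate defect that they do not measure.

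**The economic evaluation might be read as using a third contrast**, the plain after-measurement difference. The text does not show this: it names no time point and is compatible with the change contrast. It only leaves the quantity unspecified.

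**Conclusion.** The concern holds as a mismatch between the sizing and the declared main contrast, joined to a test that suits neither the contrast nor the clustering. On the article's own inputs, 18 couples per clinic per wave and a 12 v 13 split, the change contrast has between 49% and 92% power, depending on a correlation that the documents do not give. The planned single-wave comparison has 82%.

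Baseline adjustment is more powerful than the change score at every correlation. Against the after-measurement alone it gains unless the correlation is near zero, where small-sample degrees of freedom cost 1 to 2 points. The recommendation therefore does not depend on guessing the correlation.

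The change contrast is not biased in a randomised comparison; what it risks is precision. The figures use normal approximations on the risk-difference scale and ignore the stratification by IVF facilities.

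**What to change.** - **Data analysis:** replace the chi-square test of change. Define the primary effect as intervention v control adherence in the after-measurement, estimated from a multilevel logistic model with a clinic random effect and adjusted for the clinic's baseline adherence.
- **Sample size:** state that the 450 per wave refers to this after-measurement comparison, and state the power intended.
- **Economic evaluation:** state that the adherence difference in the cost-effectiveness ratio is this same adjusted difference, expressed in percentage points.

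The cost is rewording and one covariate. Both waves are already planned in all 25 clinics, so no data are added. According to the Trial status section baseline measurement is still under way, so the change can be made before any after-measurement result exists.

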### Randomization

The 25 participating clinics and their allied practitioners units will be randomized between the multifaceted implementation strategy and care as usual. Randomization will be stratified for IVF facilities (full licensed, intermediate/no IVF facilities) and will take place after all clinics have approval to participate. Randomization will be done by an independent physician and will be computer-generated. Results of the randomization will be personally communicated to all participating clinics.

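### The plain chi-square named for the main outcome conflicts with clinic randomisation, the ICC of 0.1 and the section's own multilevel statement; its true type I error could lie anywhere from about 4% to 24%

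*Protocol article*

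**What the plan says.** Under Randomization, the clinic with its allied practitioner units is the unit allocated: "The 25 participating clinics and their allied practitioners units will be randomized between the multifaceted implementation strategy and care as usual".

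Under Sample size, 450 patients in 25 clusters are derived "with an intra-class correlation (ICC) of 0.1, alpha at 5%, comparing two strategies", for an increase in adherence from 60% to 80%. That is translated into 15 to 20 patients per clinic at baseline and again at the after-measurement.

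Under Data analysis, the first sentence is general: "To analyze the effectiveness of the implementation strategy, descriptive statistics and multilevel analysis will be used". The main outcome then gets its own sentence. It is defined as the difference between baseline and after-measurement adherence, and the comparison "between the intervention and control group will be analyzed with the chi-square test". No adjustment for clinic is attached. Time to pregnancy and time to start of treatment "will be analyzed using Kaplan Meier analysis with log-rank test". Logistic and Cox regressions follow, to weigh the strategy against other predictors of adherence; clinic is not mentioned there either.

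**The concern.** A chi-square test requires independent couples. The sample size assumes that couples of the same clinic are correlated, and the clinic is what is randomised. The test named for the main outcome therefore does not match the design or the assumption that set its size.

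The section also leaves open which p-value decides the trial. A multilevel analysis and an unadjusted chi-square can lead to opposite conclusions from the same data. If the chi-square decides, chance differences between two groups of clinics may be credited to the strategy at a rate well above the stated 5%. The sample was enlarged to pay for clustering, and an unadjusted test would not make use of that protection.

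**Working it through.** **Inputs from the protocol.** Sample size: adherence 60% against 80%, alpha 5%, ICC 0.1, 25 clusters, 450 patients, 15 to 20 per clinic per measurement. Hence 450/25 = 18 per clinic. Study population: the two waves are new fertility patients from different periods, so they are different couples in the same clinics.

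**Assumptions.** Two-sided test; 80% power (not stated); equal cluster sizes; ICC 0.1 within each wave; 12 against 13 clinics in the simulations (no allocation ratio is given). The chi-square on change is read as an unadjusted test of the difference in change, with independent binomial variances.

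**1. The plan's own figure.** 60% against 80% at two-sided 5% and 80% power needs 82 per arm without continuity correction. The design effect is 1 + (18 − 1) × 0.1 = 2.7. Then 2 × 82 × 2.7 = 443, close to the stated 450. The sample size therefore fits an allowance for clustering at one measurement.

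**2. Unadjusted test on the after-measurement alone.** Actual alpha = 2 × (1 − Φ(1.96/√DE)), with DE = 1 + (m − 1) × 0.1.

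| Couples per clinic (m) | DE | Actual alpha |
|---|---|---|
| 15 | 2.4 | 20.6% |
| 18 | 2.7 | 23.3% |
| 20 | 2.9 | 25.0% |

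Simulation with 25 clinics and 20,000 runs gives 23% to 24% at m = 18.

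**3. Unadjusted test on the outcome as stated, the change.** Let ρ be the correlation between waves of the clinics' underlying adherence levels. The persistent part of a clinic's level cancels in the change, so

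DE = 1 + (m − 1) × 0.1 − m × 0.1 × ρ, which is 2.7 − 1.8ρ at m = 18.

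| ρ | DE | Alpha by formula | Alpha by simulation |
|---|---|---|---|
| 0 | 2.70 | 23.3% | 23.4% to 23.6% |
| 0.5 | 1.80 | 14.4% | 14.3% to 14.7% |
| 0.8 | 1.26 | 8.1% | 8.2% to 8.4% |
| 1 | 0.90 | 3.9% | 3.9% to 4.3% |

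DE equals 1 at ρ = 1.7/1.8 = 0.94. Below that value the test is too liberal; above it, slightly conservative.

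**4. Which repairs work.** In simulation, a t-test on clinic-level change scores held about 5% throughout. A model with both waves and only a random clinic intercept did not: a linear analogue gave 25%, 16% and 10% at ρ = 0, 0.5 and 0.8, because it leaves out the clinic-by-period variance. A small-sample correction does not restore a missing variance component.

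**The case against.** The strongest reply is that the section's first sentence promises multilevel analysis for effectiveness, and adherence is the primary effectiveness outcome. On that reading clustering is dealt with and the chi-square is loose wording. Part of this stands. A reader might infer that the protocol has settled on ignoring clustering; the text does not support that. It shows two statements that have not been reconciled. But the general sentence is not assigned to any outcome, and the main outcome is then given a specific test, so the sentence does not repair it. An unseen analysis plan is no answer either, since the article itself names the test.

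The second reply concerns size. A reader might infer that the primary test runs at about 23%. The documents do not support that as an expected value. The figure belongs to an after-measurement comparison, or to a change comparison in which clinic levels do not persist at all between waves. The stated outcome is a change in the same clinics, and some persistence is plausible. With near-perfect persistence the test is even slightly conservative. This objection stands, and it is why a range is given. It does not rescue the test, whose validity would hang on an unstated and very high between-wave correlation.

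The log-rank remark is secondary. The protocol gives no ICC for the time outcomes, so no error rate can be attached to it.

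**Conclusion.** The concern holds as an internal conflict over the primary analysis, with a named test that is not valid for the design. For the stated change outcome at 18 couples per clinic and ICC 0.1, true two-sided alpha lies between about 4% and 24%, and where it falls depends on a between-wave correlation that the protocol does not give. If the chi-square were applied to the after-measurement only, alpha would be 21% to 25% across the planned cluster sizes. A statement that standard errors are always too small would go too far, because it fails for ρ above 0.94. These figures rest on the assumptions listed with the calculation. The point must be fixed because it concerns the sole primary outcome and the trial's main conclusion.

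**What to change.** Delete the chi-square as the test for the main outcome and name one primary analysis that respects clinics. Either option below is suitable.

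- **Clinic-level.** A t-test or linear model on each clinic's change in adherence, or on its after-measurement adherence adjusted for its baseline adherence. Include the IVF-facility stratum as a covariate, with about 23 degrees of freedom or fewer (25 clinics less 2 arms, less one for each covariate term).
- **Couple-level.** A mixed logistic model with arm, period and arm-by-period terms, random clinic and clinic-by-period effects, the stratum, and a small-sample correction for 25 clusters. A random clinic intercept alone is not enough.

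As a secondary change, let the time-to-event and regression analyses also account for clinic, by frailty or clinic-robust standard errors.

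The cost is a rewording of the Data analysis section. The Trial status section says that baseline measurement is still in progress, so this can be done before after-measurement data exist. No further data are needed. The downside is that p-values may be less favourable than those of the unadjusted test.
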